### Recruitment

This prospective equivalence randomized; single-blind controlled trial protocol will be conducted among eligible participants with grade 1–2 uncomplicated euthyroid goiters. The recruitment processes will start in October 2022 and end in April 2023.

### Methods: assignment to treatment arms

This study will be a parallel trial where different groups will be randomly allocated to receive different interventions concurrently during the study.

### Randomization, blinding and allocation concealment and implementation

Patients who meet the inclusion criteria will be assigned randomly by research assistants to either local anesthesia group (L) or general anesthesia group (G) using envelope concealment. Half of these concealed envelopes will contain letter L and the other half letter G to represent LA and GA, respectively. Permuted balanced block randomization will be performed by the study supervisor to derive a random sequence of numbers that will represent the two arms in an allocation ratio of 1:1. The random sequence numbers will be generated using a web-based software (https://www.random.org/). A set of 52 numbers will be generated beginning with a minimum of 1 and maximum of 52. The numbers will then be used to label the sealed envelopes sequentially and will be concealed to research assistants. The content of the envelope will be concealed only to be opened in the operating room for the anesthesia providers to know what anesthetic technique is to be used for the research participant.

The study participants at this point in the operating room will not be blinded as the research and ethics committee considered it a moral obligation for patients to understand the nature and risks of anesthesia techniques to be used on them prior surgery.

### Blinding

The outcome data collectors will be blinded on the anesthetic technique, thus single blinding will in effect. The biostatisticians will remain blinded until interim analysis since at this stage, the insights they would offer such when to terminate the study are presumed more important to effective delivery of the trial than the uncertain extent to which they would impart bias in the face of scarce resources [30].

### Criteria for unblinding

The outcome data collectors will only be unblinded if an adverse event related to the anesthesia intervention happens and warranty disclosure to the attending surgeons and anesthesiologists.

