Following the advancement of general anesthesia (GA) techniques in which a state of unconsciousness is induced with complete absence of pain and reflexes, the number of thyroidectomies performed under GA increased and ultimately, GA became the preferred method under which thyroidectomy is carried out. In the current surgical practice, majority of surgeons prefer to perform thyroidectomy under GA which offers the advantage of pain-free surgery to the patient, thus reducing their anxiety and enabling a more relaxed operating room environment for the surgeon [8, 9].

Conversely, preference to GA is not without limitations. First, the longer recovery time from anesthesia results in prolonged hospitalization, delayed return to work, reduced patient turnover, and ultimately contributes to the unmet need for surgery. This culminates in patients presenting much later in life with huge goiters that have both local and systemic complications, compromising their general well-being, quality of life, and economic productivity. Secondly, in low-income settings with limited infrastructural and human resources, GA is comparatively undesirable due to concerns related to post-operative care and monitoring after the surgery such as lack of skilled staff and equipped intensive care units [6]. For instance, despite efforts from donor funding and south-west institutional collaborations, Uganda with its 45 million population boosts with only 100 qualified anesthesia providers (fewer than 0.05 anesthesia providers per 100,000 population) as opposed to high-income settings such as the UK with over 18 per 100,000 population [12]. Therefore, performing thyroidectomy under LA would offer the advantage of the anesthesia being administered by the surgeons themselves without putting much strain on the weak health systems.

Henceforth due to drawbacks of GA, in the last two decades, there has been an increase in the number of thyroidectomies performed under regional/LA combined with monitored anesthesia care [11, 13]. These numbers have even increased further with the development of minimally invasive thyroidectomy particularly in short-stay settings [9] and now, a few surgeons in the western world are currently doing thyroidectomies exclusively under LA [8].

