### Intervention

For group L (intervention group), as adopted from a study done by Aliyu et al. [13], infiltrative local anesthesia to achieve an anterior field block in this study will involve mixing of 0.5% bupivacaine, 2% lignocaine with 1:200,000 adrenaline.

The maximum dose of bupivacaine will be 3 mg/kg and the maximum dose of 2% lignocaine with 1:200,000 adrenaline will be 7 mg/kg [13].

The total calculated dose will be made up to 60 ml using water for injection or 0.9% normal saline; 20 ml of the mixture will be used for anterior field block which extends from the supra-sternal notch below to the cricoid cartilage above to the lateral borders of sternomastoid muscles.

Ten milliliters will be given along the incision line and another 10 ml under the investing layer of the pre tracheal fascia after raising sub-platysma muscle.

The remaining 20 ml will be given at 5 ml at each of the thyroid poles to minimize discomfort during mobilization.

Patients’ position and operative field preparation will be as in surgery under GA, but during draping, patient’s mouth and nose will remain exposed to allow continued communication and spontaneous breathing.

The communication will assure the surgeon of the safety of the recurrent laryngeal nerves.

The remaining operative steps will be carried out in accordance to the standard operative texts for thyroidectomy under GA [8, 13, 17]. In brief, the steps will include (a) positioning, painting, draping, (b) skin crease-incision and sub-platysma flap, (c) incision of investing layer of deep cervical fascia, retraction of strap muscles, and or division of middle thyroid vein, (d) superior pedicle handling, (e) recurrent laryngeal nerve and parathyroid gland safeguard, (f) thyroid gland identification and inferior thyroid vessel handling, (g) thyroid bed dissection, (h) repeat steps (f-g) on the contralateral side, (i) hemostasis with or without drain placement, and (j) wound closure.

For group G (control group), euthyroidectomy under GA will be as per the routine protocol described by Aliyu et al. [13]. Not to restrict a list of drugs that might be required in emergency situations during general anesthesia, the list is left open, and costs associated will be documented for each participant.

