### Primary outcome measures

The primary outcome measures will be early 30-day post-operative complications (harms), including: pain, nausea, vomiting, hematoma, transient voice changes, and surgical site infection rates.

The complications will be reported verbally to nursing or to attending physicians for evaluation and recorded on a questionnaire in accordance with MedDRA® version 4.21 standardized reporting on medical and surgical procedures. The post-operative pain will be measured based on visual analogue scale of 0–10 where 0 means no pain and 10 means the worst possible pain. The pain will be assessed at an interval of 6, 12, and 24 h and at 30 days. The mean pain scores will be compared at using Student’s *t*-test, assuming normal distribution; otherwise, medians will be compared using non-parametric Kruskal–Wallis rank sum test.

The nausea and vomiting will be reported to nursing or attending physicians and recorded to the questionnaire using a nausea score on a scale of 0–9 where 0 means no symptom and 9 means very severe. The symptoms will be assessed at an interval of 6, 12, and 24 h and at 30 days. The mean nausea scores will be compared using a paired Student’s *t*-test, assuming normal distribution; otherwise, medians will be compared using non-parametric Kruskal–Wallis rank sum test.

Complications: hematoma, transient voice changes, and surgical site infection rates will be assessed at 6, 12, and 24 h and at 30 days will be reported in accordance with the Clavien Dindo classification of surgical complications [27], where grade I represents complications that do not require any additional intervention, grade II requires pharmacological treatment but not radiological or surgical intervention for instance blood transfusion, grade III requires radiological or surgical re-intervention, e.g., neck exploration and hematoma evacuation, grade IV representing life-threatening complications with at least one organ dysfunction such as respiratory failure that requires intensive care admission. The difference in proportions will be compared using Wilcoxon sum rank test.

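### The unblinding rule lets outcome collectors learn the arm after an anesthesia-related event, although the clinicians to be informed already know it, so the assessor blind can be lost selectively in some patients with events

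*Protocol article*

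**What the plan says.** The Blinding section of the protocol rests the single-blind label on the assessors: "The outcome data collectors will be blinded on the anesthetic technique, thus single blinding will in effect". Trial design says the same. Participants are not blinded (Randomization, blinding and allocation concealment and implementation).

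Criteria for unblinding then sets the one exception: "The outcome data collectors will only be unblinded if an adverse event related to the anesthesia intervention happens". The sentence goes on to a second condition, "warranty disclosure to the attending surgeons and anesthesiologists", which I read as a slip for an event that warrants such disclosure. Both conditions must be met.

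The Randomization section says of the envelope content that it is "only to be opened in the operating room for the anesthesia providers to know what anesthetic technique is to be used". The Intervention section says of the local anesthesia arm that the "patient’s mouth and nose will remain exposed to allow continued communication and spontaneous breathing".

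On the endpoint, "The primary outcome measures will be early 30-day post-operative complications (harms"; the listed components are pain, nausea, vomiting, hematoma, voice change and surgical site infection. They are assessed at 6, 12 and 24 hours and at 30 days. Table 1 places satisfaction at 30 days.

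**The concern.** Emergency unblinding normally exists so that a treating clinician who does not know the allocation can learn it. Here the rule acts on a different group, the people who record outcomes, and the clinicians named as recipients are not blind. The step carries the cost of unblinding without its usual benefit.

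The trigger is also not neutral to the endpoint. An event judged to be related to the anesthetic may itself be a primary complication; vomiting and voice change are obvious candidates. Where it is, the assessor learns the arm because of the outcome, and does so while later assessments of the same patient are outstanding. What is at stake is detection bias concentrated in patients with events: the Clavien-Dindo grade given to the event, and the remaining pain, nausea, voice, infection and satisfaction entries.

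**Working it through.** The rule contains no figure to reproduce. The check sets the relevant sections side by side.

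**1. Who knows the arm when an event occurs?**

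| Party | Knows the arm? | Source in the protocol |
|---|---|---|
| Anesthesia providers | Yes, once the envelope is opened | Randomization section |
| Surgeons | Yes, from operating on an awake, communicating patient or an unconscious one | Intervention |
| Participants | Yes | Randomization section |
| Outcome data collectors | No, unless the rule is triggered | Blinding; Criteria for unblinding |
| Statisticians | No, up to the interim analysis | Blinding |

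The Introduction adds, as a general argument for the technique, that "performing thyroidectomy under LA would offer the advantage of the anesthesia being administered by the surgeons themselves". This supports the second row but is not needed for it.

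**2. Does unblinding the collector inform the clinician?** The second condition can be read in two ways.
- *The arm is to be disclosed.* The operating team already has it. A blinded collector does not hold it and cannot be its source.
- *The event is to be disclosed*, for example one found by a collector at follow-up. The collector can report an event without knowing the arm.

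On neither reading does the disclosure require the collector to be unblinded.

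**3. Does the trigger touch the endpoint?** In part. The primary components include some that an anesthetic can plausibly cause. The Adverse events section, however, attributes expected pain and complications to the surgery, and treats unusual events such as a drug reaction separately. The trigger therefore overlaps the primary outcome but is not identical with it.

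**4. What is left to assess once the blind is broken?** The schedule is 6, 12 and 24 hours and 30 days.
- Event before 6 hours: up to four assessments remain.
- Event between 6 and 12 hours: three remain.
- Event after 24 hours: the 30-day assessment remains, which includes satisfaction.

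Records completed before the event stay blinded.

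**5. Can the number of patients be derived?** No. Sample size estimation cites complication-free proportions of 83% (local) and 79% (general) and plans 26 per arm. The expected number of patients with any complication is

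26 × (1 − 0.83) + 26 × (1 − 0.79) = 4.42 + 5.46 = 9.88 of 52.

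The share that would be anesthesia-related and would also warrant disclosure is not given. If it is assumed to lie between 10% and 100%, the result is 0.99 to 9.88, or about 1 to 10 patients. That width comes from my assumption. The figure is not a firm ceiling either, because an unusual drug reaction could trigger the rule without being among the complications counted in the cited study.

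**The case against.** **The rule is narrow.** It restricts unblinding to events that meet two conditions. This stands: a reader might infer that the blind is lost whenever an anesthesia-related event occurs, and the text does not say that.

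**The trigger is not the endpoint.** A reader might infer that the two coincide. The Adverse events section points the other way, since the trigger may be aimed mainly at unusual reactions. Overlap is possible; identity is not shown.

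**The numbers do not carry the point.** It is tempting to say that about 10 of 52 patients would be unblinded and that reclassifying one moves an arm by 1/26 = 3.8 points, nearly the whole expected difference of 83 − 79 = 4 points. The documents do not support this. The 10 counts all complications. A patient whose trigger is a primary complication already counts as having one, so later knowledge of the arm cannot readily change the any-complication proportion. And the trial's stated equivalence threshold is 33 points, against which 3.8 is small; the 4-point difference decides nothing.

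**The blind is weak anyway.** Participants know their arm and report complications and satisfaction verbally, and the collectors' questionnaire includes intraoperative events (Data collection). This stands and limits what the fix can gain. It does not justify a further, avoidable breach.

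**Collectors may treat patients.** The section on adherence to the intervention protocol describes research assistants as doctors on duty, so one cannot claim that collectors never treat. The point does not need that claim: the operating team knows the arm in every case.

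**The article is condensed.** The absence of a replacement assessor may be a detail left to the full protocol, and I do not rely on it. The rule itself is stated outright.

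Nor is assessor blinding the only blinding in the trial, since the statisticians are blind up to the interim analysis. That does not protect outcome recording.

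**Conclusion.** The point holds in a limited form. The rule permits outcome collectors to be unblinded for a purpose that it cannot serve, because the clinicians to be informed already know the arm. Since anesthesia-related events can overlap the primary 30-day complications, the assessor blind can be lost selectively in some patients with events, with effect on grading and on their remaining records. Neither the number of patients nor the direction of bias can be derived from the document, and no effect on the equivalence conclusion is shown.

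The conclusion assumes that the garbled second condition means an event warranting disclosure, and that the operating team remains available as the source of the allocation. It is a modest defect, worth correcting because the correction is nearly free.

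**What to change.** Replace the trigger in Criteria for unblinding with three statements:

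- Outcome data collectors stay blinded for each participant until that participant's 30-day assessment is complete, including after an adverse event.
- The operating and anesthesia team, already aware of the arm, judges whether an event is related to the anesthetic and reports it on a form kept apart from the collectors' questionnaire.
- Any unblinding of a collector, for whatever reason, is logged with its date, so that records made afterwards can be identified.

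The cost is a change of wording and a little extra paperwork for the separate form and the log. Care is unaffected, because the treating team knows the allocation throughout. The change does not cure the wider limits of the blind, namely unblinded participants who report their own symptoms and collectors who may also be doctors on duty.

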### Methods: data collection, management, and analysis

#### Data collection

Data will be collected by the PI and trained research assistants using a pre-designed and pre-tested structured questionnaire after educating participants for the need and significancy of follow up. The data collection tool was designed in English (the official language in Uganda) with translation in local language for the illiterate. A content validity index of 78% from 15 pre-test participants was considered adequate. Parts A and B of the questionnaire on socio-demographic and grade and size of goiter will be filled and completed. Part C of the questionnaire will be filled with intraoperative events. Part D of the questionnaire will be filled post-operatively and during follow up.

### Data collection plan: retention

A pre-designed and pre-tested structured questionnaire will be used to ensure accurate data entry. Collected data will be checked for completeness before the participant leaves the interview room, data will be collected by paper questionnaire, and then double entered in Excel 2019 version to ensure completeness and will be transferred to STATA version 15.0 for further analysis.

Participants will be continuously educated to understand the significancy of the study. The data collection tool has also been made as easy to complete as possible.

### Data management and analysis

Data will be coded, entered in Excel version 2016, and later exported to STATA 14.2. for analysis. The intention-to-treat model will be used to minimize bias as way of reflecting what happens in real clinical practice. The intention-to-treat population will be used for inference and will be defined as all eligible randomized patients recruited in this study. Analysis will be done per study objective. Socio-demographic and surgical factors will be summarized descriptively using summary measures as proportions, means, medians, and measures of variation such as standard deviations for means, interquartile range for medians. All analyses will be computed at 95% confidence intervals and regarding *p* < 0.5 as statistically significant.

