### Sample size estimation

Sample size estimation in this study assumes a null hypothesis that there is no difference in early post-operative outcomes for euthyroidectomy under LA versus GA (equivalence study). In a study that evaluated the measurement of acute post-operative outcomes amongst patients who undergo surgery, a patient acceptable symptom state, i.e., the value beyond which patients considered themselves well, was documented at 33% [28]. Based on a study at the Scott and White Memorial Hospital, in Texas, the proportion of patients who underwent euthyroidectomy under LA with no identifiable complication were 83% as opposed to 79% who underwent GA [16]. Therefore, assuming a statistical power of 80%, type 1 error of 0.05, and a threshold for equivalence in effect with a dichotomous outcome that LA is no better or worse than GA by a minimal clinically important difference of 33% in the primary outcome measures; the sample size estimation based on Cleveland Clinic sample size estimation in clinical research (https://riskcalc.org/samplesize/) [29] will be 26 for each arm (1:1 allocation), including additional 10% to cater for loss to follow-up.

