## Objective one

The occurrence of early post-operative complications of euthyroidectomy under the two arms (LA and GA) of the study will be measured by total occurrence of a particular complication divided by the total number of euthyroidectomy done under LA and GA, respectively. These will be expressed as percentages with 95% confidence interval and the difference in proportions will be compared using a two-sample Student’s *t*-test, assuming normal distribution and equal variance. The Shapiro–Wilk test will be used to assess for normalcy of distribution whereas Levene’s test will be used to assess for equality of variance.

For the pain scores, visual analogue scale will be stratified as no pain (0), mild (1–3) or moderate (4–6), and severe (7–10) and the difference in proportions will be compared using non-parametric Kruskal–Wallis rank sum test (H). The overall occurrence of adverse events in both groups will be summarized as proportions in accordance with Clavien Dindo classification [27].

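### The 26 per arm fits an equivalence test at one-sided 5% per bound (a 90% CI), but the only interval level the analysis names is 95%, at which power is about 69% or less

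*Protocol article*

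**What the plan says.** The section on sample size estimation takes its rates from a cited study: "the proportion of patients who underwent euthyroidectomy under LA with no identifiable complication were 83% as opposed to 79% who underwent GA". The margin applies in both directions: "LA is no better or worse than GA by a minimal clinically important difference of 33% in the primary outcome measures". The error rates are set by "assuming a statistical power of 80%, type 1 error of 0.05, and a threshold for equivalence in effect with a dichotomous outcome", with no statement of whether 0.05 applies to each bound or is split between them. The resulting size "will be 26 for each arm (1:1 allocation), including additional 10% to cater for loss to follow-up". The randomization section agrees with 26 per arm: "A set of 52 numbers will be generated beginning with a minimum of 1 and maximum of 52". The abstract gives a different figure, 29 per arm.

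On the analysis side, the section on data management and analysis states "All analyses will be computed at 95% confidence intervals". Objective one repeats the level for the complication outcomes: "These will be expressed as percentages with 95% confidence interval". No section mentions a 90% interval or a one-sided 5% test, and none says what result would lead to a conclusion of equivalence.

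**The concern.** In an equivalence test the error rate and the interval level are tied together. A 5% type 1 error is controlled by two one-sided 5% tests, which together amount to asking whether the 90% interval lies inside the margin. Asking the same of a 95% interval is two one-sided 2.5% tests, a stricter standard that needs more patients for the same power.

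The sample size appears to rest on the first standard, while the only level offered to the analyst is the second. Two things are at stake. The stated 80% power may not be what the trial delivers. And a borderline result could be called equivalent under one section and not equivalent under another. The printed significance threshold of p < 0.5 is a separate slip; this mismatch would remain if it read 0.05.

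**Working it through.** **Inputs**, all from the sample size section: LA 0.83, GA 0.79, so a true difference of 0.04; margin ±0.33; power 80% (z = 0.8416); 10% loss. The variance term is 0.83×0.17 + 0.79×0.21 = 0.1411 + 0.1659 = 0.307. The distance to the nearer bound is 0.33 − 0.04 = 0.29, and to the farther bound 0.33 + 0.04 = 0.37.

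**Reproducing 26.** There are two usual routes, and each must be kept separate.

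- *Nearer bound only:* n = 0.307 × ((z + 0.8416)/0.29)². With z = 1.645, n = 22.57, so 23; 23/0.9 = 25.6, so 26 with loss. With z = 1.96, n = 28.65, so 29; 29/0.9 = 32.2, so 33 with loss.
- *Both bounds:* the smallest n whose two-bound power reaches 80%. With z = 1.645 this is 26 evaluable (26/0.9 = 28.9, so 29 with loss). With z = 1.96 it is 32 evaluable (32/0.9 = 35.6, so 36 with loss).

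At one-sided 5% both routes meet the stated 26, the first after loss and the second before it. At one-sided 2.5% neither does.

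**Two-bound power.** Power = Φ(0.29/SE − z) + Φ(0.37/SE − z) − 1, with SE = √(0.307/n). At n = 26, SE = 0.1087:

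- 90% interval: Φ(1.024) + Φ(1.760) − 1 = 0.847 + 0.961 − 1 = 0.808.
- 95% interval: Φ(0.709) + Φ(1.445) − 1 = 0.761 + 0.926 − 1 = 0.687.

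The same formula at other sizes gives the table below. Exact binomial enumeration with Wald limits is in brackets.

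| Evaluable per arm | 90% interval | 95% interval |
|---|---|---|
| 23 (26 × 0.9 = 23.4) | 74.7% (74.3%) | 60.2% (61.5%) |
| 26 | 80.8% (79.6%) | 68.7% (69.2%) |
| 29 (abstract, no loss) | 85.4% (86.1%) | 75.4% (77.6%) |

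If the abstract's 29 is itself meant to include 10% loss, 29 × 0.9 = 26.1, and the row for 26 applies.

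**Split decisions.** With 26 per arm at the assumed variance, an observed difference passes the 90% interval up to 0.33 − 1.645×0.1087 = 15.1 points, but passes the 95% interval only up to 0.33 − 1.96×0.1087 = 11.7 points. For example, 18/26 complication-free on LA against 21/26 on GA is a difference of −11.5 points with an estimated SE of 11.9 points. The 90% interval is −31.1 to 8.0 (inside ±33) and the 95% interval is −34.9 to 11.8 (outside). Any result that passes at 95% also passes at 90%, so the share of trials that split is the difference in power: 80.8 − 68.7 = 12.1 points at 26 evaluable, and 74.7 − 60.2 = 14.5 at 23.

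**The case against.** Four objections have weight.

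- **The one-sided 5% basis is inferred.** A reader might conclude that 26 can arise in no other way. The document does not support that. With a true difference of zero, the same variance and one-sided 2.5%, the single-bound formula gives 0.307 × ((1.96 + 0.8416)/0.33)² = 22.1, so 23, and again 26 after loss. The protocol states its null as no difference, and it relies on an online calculator whose settings are not given. This route does set aside the quoted 4-point difference and the second bound, and two-bound power at 26 with zero difference and a 95% interval is still only 71.8%. The shortfall survives, but the word *only* does not.
- **No section says that equivalence is judged by a 95% interval.** A reader might infer that the protocol prescribes this and is therefore plainly underpowered. It does not. The interval in objective one attaches to the complication percentages, and the between-arm comparison there is a t-test. The mismatch rests on the general sentence covering all analyses, so the power loss is conditional on that sentence being followed for the equivalence decision.
- **The shortfall depends on the formula.** Counting the nearer bound alone, power at 26 with a 95% interval is 76.1%. That is still below 80%, and it ignores a bound that the protocol explicitly sets.
- **A 95% interval is the more conservative choice.** It does not raise the risk of a false equivalence claim. That is correct; the cost is power and clarity.

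**Conclusion.** The point stands in conditional form. The stated 26 per arm at 80% power is consistent with one-sided 5% per bound, and the only interval level in the analysis text is 95%. If that level decides equivalence, two-bound power is about 69% with 26 evaluable and about 60% with 23, and the abstract's 29 gives about 75% if nobody is lost. None of these reaches 80%.

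Even the 90% interval does not fully secure the stated figure. It gives about 81% if all 26 are evaluable, but about 75% at the 23 implied by the loss allowance. Power therefore needs restating under either choice.

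The figures assume the protocol's rates of 83% and 79%, the complication-free proportion as the tested outcome, and the unpooled normal approximation; exact enumeration agrees within about 2.5 points. Whether 26 or 23 is the relevant row depends on whether patients with imputed outcomes are counted as fully informative.

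**What to change.** In the sample size section, state that equivalence is tested by two one-sided tests, each at 5%. In the analysis section and objective one, state that equivalence on the complication-free proportion used for sizing is concluded when the 90% interval for the LA–GA difference lies within ±33 points, and that 95% intervals are kept for all other estimates. Restate power as about 81% if all 26 per arm are evaluable and about 75% at 23.

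If the sponsor prefers the 95% interval for the equivalence decision, say so and replace 80% with about 69% (26 evaluable) or about 60% (23).

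In either case, reconcile the 26 per arm of the sample size and randomization sections with the 29 of the abstract, and say whether the final figure is before or after loss.

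The cost is a few sentences and no extra patients. The price is either a less conservative interval for the main claim or a less favourable stated power. The change also writes the complication-free proportion into the analysis, where at present only individual complications are compared. It should be settled before any between-arm results are seen.

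### The significance threshold for all analyses is written as p < 0.5, which contradicts the protocol's own type 1 error of 0.05 and its 95% confidence intervals

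*Protocol article*

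**What the plan says.** The Data management and analysis section sets one rule for the whole analysis: "All analyses will be computed at 95% confidence intervals and regarding *p* < 0.5 as statistically significant". It is the only sentence in the article that defines statistical significance.

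Two other places state an error level or a confidence level:

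- Sample size estimation: "assuming a statistical power of 80%, type 1 error of 0.05".
- Objective one, on the complication rates: "These will be expressed as percentages with 95% confidence interval".

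The sample size section also supplies the other design inputs. The margin is described as "a threshold for equivalence in effect with a dichotomous outcome that LA is no better or worse than GA" and set "by a minimal clinically important difference of 33% in the primary outcome measures". The assumed complication-free proportions are given as "with no identifiable complication were 83% as opposed to 79% who underwent GA". The result "will be 26 for each arm (1:1 allocation), including additional 10% to cater for loss to follow-up".

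**The concern.** The sentence applies to all analyses. It therefore reaches the pain and nausea scores and the complication comparisons under Primary outcome measures and Objective one, the cost comparison under Objective two, and the satisfaction comparison under Objective three. These are tests of a difference between the arms, by t-test, Kruskal–Wallis or Wilcoxon.

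A published protocol is the standard against which the results will later be read. While the line stands, a result with p anywhere between 0.05 and 0.5 could be reported as significant in formal compliance with the plan. That matters particularly here, because the stated hypothesis is that the two techniques do not differ. A literal reading would produce declared differences by chance in about half of the comparisons where none exists.

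**Working it through.** **Inputs, all from the protocol article.** Threshold 0.5 and 95% intervals (Data management and analysis). Type 1 error 0.05, power 80%, margin 0.33, proportions 0.83 (LA) and 0.79 (GA), 26 per arm including 10% for loss (Sample size estimation). The article does not say whether tests are one-sided or two-sided. Two-sided is assumed for the difference tests because that is what matches a 95% interval.

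**Step 1: does the stated sample size follow from 0.05?** The article gives no formula. The usual one for a margin on a difference of proportions, with unpooled variance, is

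n = [p1(1 − p1) + p2(1 − p2)] × (z_alpha + z_beta)² / (margin − true difference)².

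- Variance term: 0.83 × 0.17 + 0.79 × 0.21 = 0.1411 + 0.1659 = 0.3070.
- One-sided 0.05 against the bound, true difference 0.04: 0.3070 × (1.645 + 0.842)² / 0.29² = 22.57, so 23 evaluable. 23 / 0.9 = 25.6, so 26 per arm.
- One-sided 0.025 (two-sided 0.05), true difference 0: 0.3070 × (1.960 + 0.842)² / 0.33² = 22.13, so 23 evaluable and again 26 per arm.

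The stated 26 is reproduced under either reading of 0.05.

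**Step 2: could it follow from 0.5?** Same formula, same inputs:

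| Reading of 0.5 | True difference | n | Evaluable | After 10% loss |
|---|---|---|---|---|
| Two-sided 0.5 (z = 0.674) | 0.04 | 8.39 | 9 | 10 |
| Two-sided 0.5 (z = 0.674) | 0 | 6.48 | 7 | 8 |
| 0.5 on each side (z = 0) | 0.04 | 2.59 | 3 | 4 |
| 0.5 on each side (z = 0) | 0 | 2.00 | 2 | 3 |

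None comes near 26. Replacing z at 80% by z at 90%, as some equivalence formulas do, raises the largest of these only to 14 evaluable, or 16 after loss.

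**Step 3: do the threshold and the interval agree?** Two-sided p < 0.5 means |z| > 0.674, which is the same as a 50% interval excluding zero. A 95% interval uses z = 1.960, which is two-sided p < 0.05. The two halves of the sentence give different verdicts for every p between 0.05 and 0.5.

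**Step 4: what would the written rule do when there is no difference?** 100,000 simulated two-sample t-tests per setting, at 26 per arm and at the 29 per arm given in the abstract:

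| Data under the null | n per arm | p < 0.5 | p < 0.05 |
|---|---|---|---|
| Continuous | 26 | 50.0% | 5.1% |
| Continuous | 29 | 49.9% | 4.8% |
| Binary, 19% event rate (assumed) | 26 | 52.5% | 5.6% |
| Binary, 19% event rate (assumed) | 29 | 51.2% | 4.9% |

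The 19% is the midpoint of the complication rates implied by the protocol's proportions: (17% + 21%) / 2.

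**The case against.** The strongest reply is that the harm is hypothetical. The type 1 error of 0.05, the 95% in the same sentence and the 95% under Objective one all show what was meant, and a competent analyst would use 0.05. No design quantity depends on the slip. All of that stands, and it is why this is treated as an error of wording and not of design. It does not remove the need to correct the sentence, because that sentence is the stated decision rule.

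A reader might also infer more than the document supports:

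- **That 0.5 governs early stopping.** The Interim analysis section mentions differences between the groups as a possible ground for termination, but it states no p-value and does not refer to the analysis section. It leaves the recommendation to a committee acting under its ethical guidelines. The 0.05 in the sample size section is just as available to that committee as 0.5.
- **That at least one false finding among the six complications is nearly certain.** The figure 1 − 0.5⁶ = 98.4% assumes six independent tests. Nausea and vomiting are assessed together, and pain and nausea are scores taken at four time points, so this does not describe the plan. Under the same assumption the chance is already 1 − 0.95⁶ = 26.5% at 0.05, so part of it is multiplicity and not the slip.
- **That the 83% and 79% give a false-positive rate.** A t-test at 26 per arm would reach p < 0.5 in about 55% of trials with those proportions. But they are an assumed real difference in a composite, while Objective one tests each complication separately.

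**Conclusion.** The point holds as a contradiction in the current text. A threshold of p < 0.5 for all analyses cannot stand beside a type 1 error of 0.05 and 95% intervals, and nothing in the article justifies it. Read literally, it raises the chance of calling a null comparison significant from about 5% to about 50%, a factor of ten. That figure is exact for continuous test statistics and approximate for binary ones (51% to 53% in the cases run, with an assumed 19% event rate).

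It is almost certainly a typing error for 0.05. The support is the agreement of the other statements and the fact that 26 per arm is reproduced with 0.05 and not with 0.5. The reproduction rests on a standard formula that the article does not name, but no version of it tried with 0.5 exceeds 16 per arm.

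The document does not show that the interim decision, or any analysis already done, used 0.5.

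**What to change.** In the Data management and analysis section, replace p < 0.5 with two-sided p < 0.05. Suggested wording: *Confidence intervals are 95%, and a test of a difference between the arms is called significant when its two-sided p-value is below 0.05.* This should cover every difference test in the plan, primary as well as secondary and tertiary. Limiting it to the non-primary outcomes would leave the pain, nausea and complication tests without a threshold.

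The cost is one line, plus the notice that the Protocol amendments section already requires. The sample size, the data collected and the 95% intervals are unchanged. The change should be recorded as the correction of a typing error, with its date.

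How 0.05 is split in the equivalence comparison, for example by two one-sided tests with a 90% interval, should be handled separately. That would alter the 95% intervals now stated for all analyses, and the 33% margin is defined only for a dichotomous outcome, so it is not part of a one-line correction.
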